**Fig. 1 Fig1:**
[figure not shown]
Participant timeline

Table 2 shows the scheduled assessments/activities by timepoint for the study.

**Table 2 Tab2:** Scheduled assessments/activities

Timepoint	Baseline visit	Post randomisation						
		**1 week**	**6–8 weeks**	**6 months**	**11 months**	**12 months**	**18 months**	**24 months**
**Visit type/method of data collection**	**Clinic Visit**	**Remote data collection**	**Medical notes review**	**Remote data collection**	**Medical notes review**	**Remote data collection**	**Remote data collection**	**Clinic Visit**
**Assessment**								
Consent*	X							
Eligibility Assessment*	X							
Disease & treatment history*	X							
Arthritis type-specific disease activity (CDAI & DAS28-CRP or ASDAS-CRP or DAPSA) including examination of joints by blinded assessor and CRP level results from a blood test **	X							X
*Demographics**	X							
*MSK-HQ questionnaire**	X			X		X	X	X
*EQ-5D-5L questionnaire including EQ-VAS**	X					X		X
*PHQ-4 questionnaire**	X							X
*PEPPI questionnaire**	X							X
*Health resource use and costs questionnaires**	X			X		X	X	X
*CollaboRATE & SDMQ-9 questionnaires; time spent accessing patient education material**		X						
*Flare questionnaire**				X		X	X	X
Consumer health activation index (CHAI)*	X							
Single Item Literacy (SILS)*	X							
Randomisation*	X							
Training to complete remote questionnaires*	X							
Education on PIFU**	X - PIFU arm only							
Medical records review for hospital resource use*	X							X
Medical records check that patient has been booked to correct intervention*			X		X			
Medical record review intervention adherence*								X
Medical records review for flare data*								X

*Research specific activities/procedures

**Routine clinical care activities. Joint exam and blood samples for CRP level results will be done as part of routine clinical care to determine arthritis type-specific disease activity; data will be extracted from medical notes and entered into CRF

*Italicised* assessments denote completed directly by participants

### Baseline (clinic visit)

The baseline visit is a routine care visit with additional study procedures.

Once informed consent for study participation has been obtained and eligibility confirmed, baseline data will be collected/recorded by the site research team in accordance with the data collection schedule.

A physical examination of the joints will be conducted and a routine clinical C-Reactive Protein (CRP) test will be performed to calculate the specific disease activity score. Both the physical exam of the joints and CRP test will be done as part of routine care and the resulting data will be extracted from the medical notes to the study CRFs.

Participants will be asked to complete the baseline questionnaires prior to randomisation. Usually these will be completed on a study tablet-device, but in case of problems, paper copies should be completed and subsequently entered onto REDCap by the site research team. The Consumer Health Activation Index (CHAI) and Single Item Literacy Screener (SILS) will be administered verbally to the participant by the site research team prior to randomisation and then entered into the study REDCap data collection system.

Participants will then be randomised, with those allocated to the PIFU arm being provided with verbal and written information on PIFU and how to access advice if needed.

Participants will be asked whether they wish to complete follow-up questionnaires electronically via a link sent by email, via a link sent by SMS, on paper with postal return, or during a telephone call with the central study team. At, or following the baseline visit, data on hospital resource use from 12 months prior to baseline visit to date will be extracted from the participant’s medical notes and entered into REDCap by a member of the site research team.

### 1 week post randomisation (remote data collection only)

All participants will be asked to complete questionnaires about shared decision-making discussions around their suitability for PIFU using the CollaboRATE & 9-item Shared Decision Making Questionnaire (SDMQ-9) questionnaires and time spent accessing patient education materials.

### 6, 12, and 18 months post randomisation (remote data collection only)

Participants will be asked to complete the questionnaires specified in Table 2 remotely.

### 24 months post randomisation (clinic visit)

Participants will attend a clinic visit. The 24-month visit is a routine care visit with additional data collection for the study. Participants will be asked to complete the questionnaires as specified in Table 2 remotely. If the questionnaires have not been completed prior to the clinic visit, questionnaires are to be completed during the visit.

A physical examination of the joints will be conducted and a blood sample will be collected and sent to the local site laboratory for testing for CRP level to calculate the specific disease activity score. Both of these assessments are done as part of routine care and the resulting data will be extracted from the medical notes to the study CRFs. Data on disease status, flares, hospital resource use and intervention adherence (change from PIFU to standard care or vice versa) will be extracted from the participant’s medical notes and entered into REDCap.

### Study questionnaires

Questionnaires at follow-up time points will be completed remotely. Participants will select how they would like to complete study questionnaires at the time of consent — email link, text message (SMS) link, post or telephone. For those opting to complete electronically, a link will be sent to a participant either by email or SMS to a questionnaire which is unique to a participant and their timepoint/questionnaire in the study.

Where participants opt to complete paper-based questionnaires, these will be returned to the CTU by post using the prepaid envelope provided and data will be entered into REDCap by the central CTU study team. Data collected during telephone calls with the participant will be entered directly into REDCap by the central study team.

Where required, participants will be sent up to two reminders via their preferred method of questionnaire delivery. Due to the primary endpoint being collected via questionnaire, if the questionnaires are not completed after two reminders have been sent, a further final request to complete will be made by a different method via telephone or post. The questionnaires required at 24 months may be completed during the 24 month study visit if not completed prior to the visit.

For questionnaires completed remotely, if not all questionnaires have been completed the CTU study team will contact the participant to request completion of the remaining questionnaires. No more than 1 further reminder to complete the remaining questionnaires will be sent. (Note: if during the study, a participant wishes to change how they are contacted regarding the questionnaires, this is possible and should be recorded in REDCap).

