### Sample size {19}

Three hundred and fifty participants providing data on the MSK-HQ score measured at 24 months post randomisation (175 per group) will provide 90% power to detect a difference in means of minimally clinically important difference (MCID) of 4 points [18], assuming a standard deviation of 11.5 points, using a two group t-test with a 5% (2-sided) significance level. This has been inflated to 438 (219 per arm) to allow for 20% attrition and crossover.

The MCID, estimated using the standard error as no anchor-based estimates were available [18], and the standard deviation of 11.5 points is estimated using Healthcare Quality Improvement Partnership (HQIP) National Audit for Early Inflammatory Arthritis Audit data [19]. There are no similar studies on which to base the estimated attrition rate, 20% is chosen to be conservative and in line with the wider RCT literature.

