### Sequence generation: type of randomisation {21b}

Consented participants will be randomly allocated (1:1) to one of the study arms. Randomisation will be performed using a minimisation algorithm to ensure balance between the two arms using stratification factors:Participant disease presentation (either predominantly axial, or predominantly peripheral involvement according to treating clinician)Recruiting site

Stratification by participant diagnosis will ensure that the arms are balanced in terms of their pattern of disease, as these are associated with different prognoses. Stratification by recruiting site will ensure that the treatments are balanced according to the different demographics of the cohort seen at different centres and according to the difference in practice associated at a local level for the standard care (comparator) arm.

Classification of participants as axial or peripheral will be done by their treating clinician based on their clinical assessment.

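### A partly completed questionnaire set with the MSK-HQ missing is chased less than a complete non-return, and no MSK-HQ-only request is provided

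*Protocol article*

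**What the plan says.** The section Study questionnaires sets two routes for chasing follow-up data.

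- **Nothing completed.** Up to two reminders go out by the participant's preferred method. After that, "a further final request to complete will be made by a different method via telephone or post". The stated reason is that the primary endpoint is collected by questionnaire.
- **Some, but not all, completed remotely.** The trials unit contacts the participant about the outstanding forms, and then "No more than 1 further reminder to complete the remaining questionnaires will be sent". No switch of method is described, and nothing depends on which form is missing.

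The same section, and the section on the 24-month clinic visit, provide for outstanding month-24 questionnaires to be completed at that visit. Table 2 shows months 6, 12 and 18 as remote data collection only.

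Under Statistical methods {27a}, the primary model takes MSK-HQ scores from 6, 12, 18 and 24 months. The section on missing data {27c} analyses available data. On the 20% allowance for attrition and crossover, Sample size {19} says: "There are no similar studies on which to base the estimated attrition rate".

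**The concern.** The reason given for the longer route applies just as well when the MSK-HQ is the one form missing from an otherwise returned set. Yet that participant, who is still engaged with the study, meets a firm upper limit and no change of method. Because the rule is worded as a cap, a study team that wanted to chase a missing MSK-HQ harder would be departing from the protocol.

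At stake are MSK-HQ scores that might have been obtained. Scores at 6, 12 and 18 months give the treatment effects at those times, feed the area-under-the-curve summary, and help the primary model with participants whose month-24 score is missing. Each avoidable gap makes the result lean more on assumptions about the missing data.

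**Working it through.** **1. Contacts after the initial invitation, counted from Study questionnaires and the 24-month visit section**

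| | Nothing returned | Part returned, MSK-HQ missing |
|---|---|---|
| Reminders or contacts | 2 | 1 (trials unit contact) |
| Last step | 1, by a different method | at most 1, no change of method stated |
| Total at months 6, 12, 18 | 3 | 2 |
| Clinic visit at month 24 | +1 | +1 |
| Total at month 24 | 4 | 3 |

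The gap is one contact and the switch of method. At month 24 the visit is open to both groups, so the gap matters there only for those who do not attend.

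**2. The plan's own sample size**

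Inputs from Sample size {19}: "minimally clinically important difference (MCID) of 4 points", "assuming a standard deviation of 11.5 points", "using a two group t-test with a 5% (2-sided) significance level", 90% power. Allocation is 1:1 (section {21b}).

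- Normal approximation: n per arm = 2 × (1.960 + 1.282)² × 11.5² / 4² = 173.7, so 174.
- Exact two-sample t-test: 174.67, so 175 per arm. The noncentrality at 175 is 4 / (11.5 × √(2/175)) = 3.25, and power is 0.9005.
- Inflation: 350 / (1 − 0.20) = 437.5, so 438, or 219 per arm.

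The stated figures reproduce. Nothing is wrong with the sample size.

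**3. How sensitive power is to further month-24 loss**

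The article gives no rate for sets returned without the MSK-HQ, so the extra loss below is an assumed range, not an estimate. Analysed n per arm = 219 × (1 − 0.20 − extra), on the same t-test.

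| Extra loss (assumed) | Participants, of 438 | n per arm | Power |
|---|---|---|---|
| 0 | 0 | 175.2 | 0.901 |
| 1 point | 4.4 | 173.0 | 0.897 |
| 2 points | 8.8 | 170.8 | 0.894 |
| 5 points | 21.9 | 164.3 | 0.882 |
| 10 points | 43.8 | 153.3 | 0.859 |

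For the cap to cause loss at month 24, a participant must return a set without the MSK-HQ, fail to supply it after two contacts, and also miss the visit. That combination points to the top rows. The t-test basis gives no credit for the 6- to 18-month scores, so it cannot show what is lost when those are missing.

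**4. What can still be changed**

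Trial status gives recruitment from 21 March 2025 to 31 January 2026. Adding the follow-up intervals, month 12 falls from March 2026 to January 2027, month 18 from September 2026 to July 2027, and month 24 from March 2027 to January 2028. The article is dated 4 July 2026, so at that date part of month 12 and all of months 18 and 24 were still to come.

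**The case against.** The strongest reply is the month-24 visit. The primary time point has an in-person backstop that works whichever reminder route was followed, so a reader who infers that month-24 primary data are simply lost goes further than the text allows. This stands for everyone who attends.

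Other stronger readings also fail:

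- A reader might take the cap to mean a single reminder. The word *further* follows a contact by the trials unit, so the count is two.
- A reader might infer that the final request demands the whole set. The article does not say what that request contains, and one of its two methods is a telephone call. The fair point is only that no MSK-HQ-only option is stated.
- A reader might apply a recovery fraction to the 438 − 350 = 88 participants allowed for. That has no basis in the document. The 20% covers crossover as well as attrition, and participants who cross over remain in the intention-to-treat analysis.

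The wording can also be read more generously: non-completion might include partial completion, or the one further reminder might come on top of two already sent. The gap would then shrink or vanish. On the first of these readings, however, the section tells staff both to make a final request by another method and to stop after one reminder, so it would still need clarifying.

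Finally, reminder settings and form order often sit in a data management plan, and limiting contacts limits participant burden. Both are fair. But the cap is stated in the article itself, and the change asks for one more contact only where the primary measure is missing.

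**Conclusion.** The point holds in a limited form. The article fixes a shorter chase for a partial return (two contacts, no stated change of method) than for a full non-return (three, with a change of method), and does not exempt the case where the missing form is the MSK-HQ. It describes no MSK-HQ-only fallback.

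The exposure is mainly the 6-, 12- and 18-month scores, plus participants who do not attend at month 24. Its size cannot be computed from the document and is probably small: even an assumed 2 percentage points of extra month-24 loss would take power only from 0.901 to 0.894. The sample size and the analysis model are unaffected. The conclusion rests on reading the two routes as separate, which is the natural reading. It is a cheap improvement in data completeness, not an error in the plan.

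**What to change.** In Study questionnaires, and in the data management plan and REDCap reminder settings that implement it, state that:

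1. when the MSK-HQ is missing from a partly completed set, the full non-return route applies: two reminders, then a request by a different method. The existing cap stays for all other missing forms;
2. the final request may be for the MSK-HQ alone, particularly for participants who do not attend at month 24.

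The cost is one extra contact for a few participants and a change to the reminder settings. Those who take the short option give no secondary questionnaire data at that time point. By Table 2 that means resource use and flares at months 6 and 18, with EQ-5D-5L added at month 12, and PHQ-4 and PEPPI as well at month 24. The short option should therefore be offered only at the last step, after the requests for everything outstanding have failed. Eligibility, treatment, sample size and analysis do not change.

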### Arthritis type-specific disease activity score

The disease activity score corresponding to the type of arthritis the participants have is to be completed as follows:Rheumatoid Arthritis (RA): Clinical disease activity index (CDAI) and disease activity score (DAS28-CRP)Axial spondyloarthritis (axSpA): Axial spondyloarthritis disease activity score (ASDAS-CRP)Psoriatic Arthritis (PsA) & undifferentiated arthritis: Disease activity in psoriatic arthritis (DAPSA)

If a site’s usual practice is not to repeat the CRP due to a recent test result being available, or there being no medical need to repeat (i.e. arthritis appears stable) then a further CRP result is not required for the purpose of the study.

The joint examination component is to be completed by a blinded assessor whenever possible. The blinded assessor may be a suitably trained member of the clinical or research study team.

### Qualitative sub study

A qualitative sub study will collect qualitative data from three groups — patients with inflammatory arthritis who decline to participate in the TaILOR study, patients with inflammatory arthritis who participate in the TaILOR study and who are randomised to PIFU; and NHS professionals involved in their care (clinicians, nurses, research nurses, allied health professionals, managers, administrative staff). At the site feasibility stage, we will perform a survey of all sites to collect information about their hospital and the local implementation of PIFU. This will be used to support the sampling for the qualitative studies.

### Surveys of those who decline to join the study

Those who choose not to participate in the TaILOR study will be invited to complete an anonymous, short survey about why they chose not to take part. The survey comprises a mix of closed and open-ended questions exploring reasons for declining to take part in TaILOR specifically and/or research more generally. These patients will be given an invitation letter by the site staff at the time they decline to participate. The invitation letter explains why we are asking them to complete the survey and will contain a QR code to a short survey that they can choose to complete electronically. If requested, the site can provide a paper copy of the questionnaire for the participant to complete. No further contact will be made about completion of the optional survey.

### Participant interviews

Interview topic guides for all groups will be designed in collaboration with patient research partners and the study team. All who accept the invitation to take part will be offered the choice of an online or telephone interview. For the participant qualitative interviews, interpreters will be provided if required, so that participants can be interviewed in the language of their choice. Alternatively, if the participant prefers a family member or friend can act as interpreter. All interviews will take place over Teams or telephone and be audio-recorded, transcribed and de-identified. Data will be transcribed by a General Data Protection Regulation (GDPR) compliant, University of the West of England (UWE) approved, third party supplier with a data processing agreement in place. The de-identified transcripts will be kept for 4 years and then destroyed.

We will develop a purposive sampling framework and invite patients to take part in up to two qualitative interviews. Detailed baseline data collected for the study including randomisation allocation will support the purposive sampling framework. We will aim to include patients from at least 10 different sites with a mix of age, diagnosis, disease duration, gender, ethnicity, education, income, work status, health literacy and patient activation (as defined by participant SILS and CHAI questionnaire scores). We anticipate collecting data from approximately 45 interviews from approximately 30 patients in total but will continue with interviews until data saturation is met to ensure that we identify themes from a varied sample. This large sample size reflects the diverse sample that we aim to include.

Participant data for those who take part in the qualitative portion of the study will be identified using their TaILOR identification code held in a database at UWE which contains no identifiable information. A linkage document used to identify participants will be stored at UWE in a separate, password-protected document. This will only be accessed by the qualitative team at UWE.

The interview(s) will take place between 2 and 12 weeks and/or 16–24 months after randomisation with each interview lasting between 30 and 60 min. Where possible and willing, the participants will be interviewed at both time points but if insufficient participants are willing to take part in both interviews, participants may be interviewed at just one of these time points. It is not anticipated that participants will find the questions upsetting. However, participants can stop or pause the interview at any time if they are uncomfortable. Additionally, the PIS provides contact information of disease specific charities if further support/information is required. The qualitative research team have undertaken Good Clinical Practice (GCP) training and understand the need to be responsive to participants’ needs. In the interviews, we will explore patients’ views and experiences of:Being invited to move to PIFU, including shared decision-making Acceptability of PIFU and facilitators to implementationAny consequences and perceived negative impacts of the approachIndividual and system level barriers and facilitators to accessing timely, safe and helpful care in the PIFU systemSelf-management and the impact of PIFU on their health

Optional consent to be invited to a maximum of two qualitative interviews will be collected as part of the consent form to participate in the TaILOR Study. The TaILOR qualitative research team will then contact participants directly with further information about the interviews, obtain consent to be interviewed prior to the first interview and arrange and carry out the interviews. Site staff and central CTU team will not routinely be informed as to whether a participant has taken part in a qualitative interview.

### Health professional/service provider interviews

We will invite approximately 25 health professionals and service providers to take part in qualitative interviews from 12 to 15 of the 32 sites participating in the main study. Health professionals (clinicians, nurses, research nurses, allied health professionals) and service providers (managerial and administrative team such as clinic booking staff, departmental and operational managers) are eligible to take part in the qualitative interviews provided they are willing to give consent. Sites will be selected to include a mix of rheumatology departments in larger teaching hospitals and smaller district hospitals, serving urban and rural communities, a range of socio-economic groups (based in the English indices of deprivation 2019 data) and different geographical areas. Across sites, we will sample for variation of individuals in profession/role and years working in rheumatology.

In the interviews, we will explore health professionals/service providers’ views and experiences of:The benefits and challenges of implementing PIFU in their service/at their site.PIFU education and potential ongoing unmet needs in terms of materials.Inviting patients to move to PIFU, including their perceptions of which patients are most and least likely to benefit and why.

Site staff involved with the TaILOR study will be made aware of the option to participate in an interview during the Site Initiation Visit. If the site is selected to be part of this aspect of the study, and once the site has been opened to recruitment for a minimum of 12 months, the site team will be approached to ask if there are 1 or 2 members of the team who are willing to consent to be interviewed. Further information on the interviews will be provided and those willing to be interviewed will contact the TaILOR qualitative research team directly to inform them. The TaILOR qualitative research team will then contact those health professionals/service providers selected for interview and provide the PIS and consent form. Participants will be asked to complete and return the consent form to the qualitative team ahead of the interview.

Consent will be obtained prior to starting the interview and before any data collection. Interviews should take between 20 and 40 min and participants can stop or pause the interview at any point if they become uncomfortable.

